### 3. Study Design

We plan to use a Randomized Step Wedge Cluster Design (R-SWCD) to evaluate the effect of the peer comparison feedback report on antibiotic prescribing (BS-HO group). The study will be conducted in 4 hospitals (clusters) in Atlanta, Georgia. Of note, pending discussion with Hospital Medicine Leadership, the intervention may also be rolled out at an additional hospital, although lack of retrospective data would not allow inclusion of this facility in the full analysis. Hospitals will begin in the control condition and end in the intervention condition, wherein, all hospitals will receive the intervention and cross over to the intervention arm in a random order (Figure 1). Randomization will occur at the hospital level rather than at the provider level to avoid contamination and spillover effects. Providers within a hospital are not fully independent of each other, groups tend to form because of certain selection factors, and so providers tend to be more similar to each other with respect to potential confounders.

Outcomes linked to the same provider will be assessed repeatedly on a bi-monthly bases in each hospital over a two-year time period (2023-2024). Hospitals will cross-over to the intervention arm sequentially, resulting in 4 steps with an equal step length of 2 months. Following a baseline period (January 1 - June 30, 2023), the first cluster will begin the intervention on July 1, 2023. The final cluster will transition by March 1, 2024, with intervention continuing through December 31, 2024 in all hospitals.

A step wedge design, which involves the randomized and sequential roll out of the intervention to hospitals over time was chosen as it can model and adjust for any underlying temporal trends and results in all hospitals receiving the intervention **which is desirable from a healthcare quality improvement and antimicrobial stewardship perspective**. Randomization of the order of implementation reduces confounding from baseline cluster-level factors. Lastly, gradual roll out of the intervention will allow us to identify and address any implementation bottlenecks.

**Figure 1.** Stepped-Wedge interventional study design. Abbreviations: E, educational session; PF, Provider Feedback. Grey boxes reflect intervention periods with bi-monthly PF reports.

|            | 2023       |        |        |        | 2024   |        |               |
|------------|------------|--------|--------|--------|--------|--------|---------------|
|            | Jan-Jun 23 | Jul-23 | Sep-23 | Nov-23 | Jan-24 | May-24 | Jul to Dec 24 |
| Hospital A |            | E + PF | PF     | PF     | PF     | PF     | PF            |
| Hospital B |            |        | E + PF | PF     | PF     | PF     | PF            |
| Hospital C |            |        |        | E + PF | PF     | PF     | PF            |
| Hospital D |            |        |        |        | E + PF | PF     | PF            |
| Hospital E |            |        |        |        |        | E + PF | PF            |

#### **4. Study Population and Sample Size**

The study will focus on hospitalists as the primary antibiotic prescriber. The list of hospitalists will be identified and fixed at study onset and updated semi-annually. Updates from Hospital Medicine Service Administration will be obtained on any staffing changes, although staff turnover is not expected to exceed 10%. A secondary analysis may be performed on new staff who join during the study implementation phase. Hospitalists typically do not practice in more than one hospital and so we do not expect any contamination across hospitals. The study will exclude nocturnists (night-shift hospitalists) as they have less control over antibiotic prescribing ( $n = 11$ ; 8% of all hospitalists). The final study sample will include a total of 125 hospitalists (15-40 hospitalists per hospital) across 4 Emory hospitals.

#### **5. Study Measures and Outcomes**

Data from January 2023 to December 2024 will be extracted for inpatients at all hospitals with Hospital Medicine Services. For each hospitalist, billing data will be used to identify patient encounters and to calculate billed patient-days (bPD). Antibiotic prescribing data from electronic medication administration records (eMAR) will capture days of antibiotic therapy (DOT) for NHSN-defined broad-spectrum hospital-onset (BS-HO) agents per bPD.

Patient characteristics linked to each encounter will include age, microbiology results (e.g., bacteremia), ICD-10–based antibiotic indications (e.g., pneumonia, COVID-19, sepsis, urinary tract infection), and comorbidities, enabling calculation of Elixhauser comorbidity indices. Generalized linear models will be used to generate provider-level observed-to-expected ratios (OERs). In each model, bPD will remain continuous, while other predictors will be categorized by quintiles based on their relationship with DOT. Based on input from Hospital Medicine Services leadership and focus groups, hospital-specific models will be used to calculate OERs in order to maximize provider credibility of the metric.

The primary outcome will be the observed provider-specific antibiotic prescribing rate, defined as billed DOT of BS-HO antibiotics per 1,000 billed patient-days. This measure alone will not be risk adjusted; however, patient- and provider-level characteristics will be adjusted for and included as covariates in the regression model described below. For illustrative (descriptive) purposes, risk-adjusted provider-specific OERs will also be estimated, with point estimates (means) and variance plotted over time by facility. OERs will not be modeled directly as regression outcomes.

## **7. Statistical Analysis**

**For the primary outcome analysis,** a generalized linear mixed-effects model with a negative binomial distribution and log link will be used to evaluate the effect of the intervention on antibiotic prescribing rates over time. The observed DOT will be modeled as a function of provider receipt of feedback reports, time (bimonthly period) to account for secular trends and time-varying confounding, and a random facility effect to account for clustering of providers within hospitals. A random intercept for each provider nested within facility will be included to account for correlation among repeated observations and the hierarchical data structure. The intra-cluster correlation coefficient (ICC) will be estimated to quantify the proportion of total variance attributable to between-cluster differences. Models will adjust for patient-mix characteristics as covariates.

Sensitivity analyses of the primary outcome will be conducted among the subset of providers who indicate that they received and reviewed the feedback reports, to account for potential implementation bias.

**Secondary outcomes will be analyzed at the patient level** among all patients receiving care from hospital medicine services and discharged with ICD-10 codes for pneumonia or urinary tract infection, as this group is expected to be most vulnerable to changes in antibiotic de-escalation practices. Safety outcomes will be analyzed using generalized mixed-effects logistic regression models to evaluate intervention effects over time, accounting for repeated hospitalizations within patients and clustering by facility. Covariates will include time (to account for seasonality) and patient-level indicators (COVID-19, influenza, Elixhauser comorbidity index, and sepsis). All analyses will be performed using R Statistical Software (version 4.2.0; R Core Team, 2021).

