## Analysis Plan and Outcomes.

Primary outcome is the provider-specific SAR, separately for each antibiotic grouping. Secondary outcomes include CD, readmission (< 30 days of discharge), length of stay. Changes in 2-month SAR will be estimated using an interrupted time series analysis, evaluating changes in each antibiotic grouping separately, analysis will consider hospital fixed effects. Secondary outcomes will be analyzed at the patient level among all billed encounters using logistic or negative binomial regressions. Inclusion of provider and quarter-year fixed effects will control for time-invariant provider and site characteristics and secular time trends (e.g., seasonal patient mix) and establish a difference-in-difference framework. This approach will estimate the within-provider change in patient outcomes, pre- and post-intervention. We will control for patient (e.g., sex, age, Comorbidity Index) mix, time-variant provider (e.g., census) factors.

Data Sources: The primary source of data will be the EH Clinical Data Warehouse (CDW), a repository that integrates data from multiple clinical applications within EHC and has flexibility to create customized, research-specific metrics. Outcomes for Aim 2 will also be calculated from data elements within the EH CDW (i.e., re-admissions, length of stay.)

Provider-specific SARs. Data elements will be aggregated into 2-month intervals for each of the 147 hospitalists across each hospital. Billed Days of Therapy (bDOT) and billed patient-days (bPD) derived for each antimicrobial group will be limited to the eligible dates of each patient encounter to dates billed by a hospitalist (bPD). For each period, a SAR will be determined from provider specific bDOT calculated along with predicted DOT using preliminary regression models. Regression models will be created from analyzing summary provider specific data and providers' encounter data for each 2-month period of the baseline period. Encounter summary data will be aggregate number of encounters billed by

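### The primary model has no hospital-by-period variance and no small-sample method for 4 randomised hospitals, so a nominal 5% test is not protected against hospital-specific shocks

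*Combined protocol and SAP*

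**What the plan says.** SAP section 3: "The study will be conducted in 4 hospitals (clusters) in Atlanta, Georgia". "Randomization will occur at the hospital level rather than at the provider level to avoid contamination and spillover effects". The roll-out is described as "resulting in 4 steps with an equal step length of 2 months", within data covering 2023 and 2024.

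SAP section 4: "The final study sample will include a total of 125 hospitalists (15-40 hospitalists per hospital) across 4 Emory hospitals".

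SAP section 7 regresses observed days of therapy on receipt of feedback, bimonthly period and patient mix. It adds two random terms: "a random facility effect to account for clustering of providers within hospitals", and an intercept for each provider nested in facility. An ICC is to be estimated from the data. The one sensitivity analysis of the primary outcome restricts to providers who say they read the reports, which leaves the correlation structure as it was. Section 7 names no hospital-by-period term, degrees-of-freedom correction, cluster-robust variance or randomisation test. The safety models are described as "accounting for repeated hospitalizations within patients and clustering by facility".

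Neither document gives a significance level or says whether tests are one- or two-sided. The Sample Size entry of the protocol's Study Summary gives only 80% power.

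**The concern.** In a stepped wedge the treatment indicator changes by hospital and period. The noise that competes with the treatment contrast is therefore whatever moves one whole hospital in one period and is not shared by the others, such as a local staffing, formulary or supply change. All hospitalists at that site share such a shock.

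The planned random effects cannot represent it. The hospital intercept is a level held for two years, the provider intercept is the same at a lower level, and the period effect moves all hospitals together. What is left goes into the provider-period residual, which the model treats as independent across the 15-40 providers of a hospital. The standard error of the intervention effect is then too small, and an ineffective programme can be declared effective more often than the nominal rate.

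**Working it through.** **The plan's own figure.** The only design figure is 80% power for an effect size of 0.9-1.1 with 147 providers, said to allow for clustering. Assuming a two-sided 0.05 test and no clustering, 147 providers give over 99.9% power; 26-40 would be enough for 80%. To bring 147 down to 80% needs an ICC of about 0.075 (effect 0.9) to 0.13 (effect 1.1). The documents give no ICC, so the figure can be neither confirmed nor refuted, and it does not help here.

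**Inputs from the documents.** 4 hospitals; 125/4 = 31.25 providers per hospital on average; 24 months / 2 = 12 periods; 4 x 12 = 48 hospital-period cells.

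**Assumptions.** The analysis is approximated as Gaussian on the log rate. s is the residual SD of a provider's two-month log rate and w is the hospital-by-period SD left after the period effect and covariates. The documents give neither, so both are shown as ranges.

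**Formula.** The model takes the variance of a cell mean as s²/31.25; the true value is s²/31.25 + w². With r = √[(s²/31.25 + w²)/(s²/31.25)], the type I error of a nominal two-sided 5% test is 2 x [1 − Φ(1.96/r)].

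Example, s = 0.40 and w = 0.05: s²/31.25 = 0.16/31.25 = 0.00512; w² = 0.0025; r = √(0.00762/0.00512) = 1.220; 1.96/1.220 = 1.607; type I error 10.8%.

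| Residual SD s | w = 0 | 2% | 3% | 5% | 10% |
|---|---|---|---|---|---|
| 0.30 | 5.0% | 6.6% | 8.7% | 15.2% | 35.4% |
| 0.40 | 5.0% | 5.9% | 7.1% | 10.8% | 25.4% |
| 0.50 | 5.0% | 5.6% | 6.3% | 8.7% | 19.1% |
| 0.60 | 5.0% | 5.4% | 5.9% | 7.6% | 15.2% |

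The formula ignores the small part of the shock that the fitted residual variance absorbs, so it runs slightly high at large w. Simulation of a balanced linear analogue at s = 0.40 gave 6.9%, 10.4% and 23.0% for w = 3%, 5% and 10%.

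**Check with fitted mixed models.** REML fits used a random hospital effect, a random provider effect and fixed periods, with s = 0.25, provider SD 0.15, an assumed split of 40/38/32/15 providers, and about 900 runs per scenario. At hospital SD 0.2 they gave 4.8%, 8.3%, 20.2% and 42.2% for w = 0, 2%, 5% and 10%. SAP section 3 puts the last crossover at March 2024, while its Figure 1 has Hospital D at January 2024. In the closed form the choice changes type I error by at most 0.1 point.

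**Does the repair work?** Adding a random hospital-by-period term and a t reference on 48 − (4 + 11 + 1) = 32 df gave 3.3% to 6.4% in the same REML fits (simulation SE about 0.7 points). If shocks are autocorrelated (0.7 between adjacent periods), a cell-mean analysis on 32 df gave 5-8%. A randomisation test over the 4! = 24 hospital orders stayed at 3.6-4.5%; its smallest P value is 1/24 = 0.042.

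**Power after the repair.** A 10% reduction is 0.105 on the log scale. Weighted least squares on the 48 cells (s = 0.25, January 2024 last crossover, averaged over the 24 orders) gives SEs of 0.0347, 0.0475 and 0.0768 at w = 2%, 5% and 10%. Power ≈ Φ(0.105/SE − 2.037) is then about 84%, 57% and 25%.

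**The case against.** The strongest reply is that the inflation rests on a variance nobody has documented. At w = 0 there is none, and at 2% it is about one point. Period is in the model, so a respiratory wave or shortage common to four Atlanta hospitals is absorbed if period is categorical. Patient-mix covariates may take up part of the rest. Residual noise could also exceed 0.40. The protocol's preliminary data give 437,303 billed patient-days over 116 hospitalists and 18 two-month periods, or about 209 per provider-period, and the outcome is a single antibiotic group. At s = 0.50-0.60 a 5% shock gives 7.6-8.7%. All of this stands, and it makes the size conditional. It does not supply the missing term, and nothing in the plan would reveal whether the term was needed.

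A reader might infer more than the documents support:

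- *A stated 5% error rate is breached.* No rate is stated.
- *Having only 4 random hospital intercepts inflates error.* With w = 0 the fitted models gave 4.8-5.6%. The contrast is mostly within hospital. The small number of hospitals matters for the degrees of freedom and for estimating the added variance.
- *The preliminary SAR interquartile range of 0.9-1.1 supplies the residual SD.* It describes adjusted 2016-2018 SARs and does not separate stable provider differences from period-to-period noise, so it is not used.
- *The protocol's fixed effects contradict this model.* The protocol says "analysis will consider hospital fixed effects", in an interrupted time series of SAR. That is a separate wording difference and no evidence of inflation.
- *The safety models are shown to be too liberal.* They lack the same term, but nothing was computed for patient-level binary outcomes.

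**Conclusion.** The gap is real and its size is conditional. The treatment is assigned by hospital and period, the model has no variance at that level, and no small-sample method or randomisation check backs it up. A nominal two-sided 5% test is therefore not protected. At residual SD 0.30-0.40, error is 5% with no hospital-by-period variance, 5.9-6.6% at SD 2%, 7-9% at 3%, 11-15% at 5% and 25-35% at 10%; it is lower if residual noise is larger. The figures rest on a Gaussian approximation to the negative binomial model, about 31 providers per hospital, no provider turnover and assumed SDs. The mechanism is well supported; confidence in the magnitude is moderate. It matters because hospital-specific swings of 5-10% would be of the same order as the 10% reduction the protocol aims to detect.

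**What to change.** In SAP section 7:

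1. State alpha and sidedness.
2. Enter bimonthly period as a 12-level factor.
3. Add a random hospital-by-period intercept to the primary model and refer the intervention effect to t on about 32 df. Analysing the 48 hospital-period adjusted log rates on the same df is an alternative.
4. Pre-specify a randomisation test over the 24 hospital orders as a check, since autocorrelated shocks can leave 5-8% error after step 3. It is coarse: with a smallest P of 0.042, only the most extreme order can reach 5%.
5. Put the same term in the safety models for consistency, and say that its effect there has not been quantified.

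Whether hospital is fixed or random is largely preference; align the protocol and SAP wording separately.

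The drafting and programming are small. The real cost is wider intervals and, if the shocks exist, lower power: about 84%, 57% or 25% for a 10% reduction at hospital-by-period SD 2%, 5% or 10% (residual SD 0.25). If the variance proves negligible, little is lost.

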## Study Intervention/Investigational Agent

No Drug or Device is being used for this intervention.

Primary intervention.

The intervention is messaging to hospitalists via email every 2 months (bi-monthly) that contains peer comparison data of the previous 2 months and antibiotic prescribing educational content. Draft content of this message is submitted.

The detail of the content is still to be developed, but may include a relative rank in prescribing metrics, with blinding to specific Peers' identity, with department wide and facility specific goals highlighted. Those in the lowest prescribing quartile will earn the designation of "Top Performer". The usual care arm will be an educational email about simple steps to improve antibiotic prescribing sent bimonthly to all hospitalists.

Secondary Intervention (if needed).

An interim analysis will occur at the facility-level after three quarters (9 months) of intervention data to determine if high prescribers (i.e., SAR above 1.25, or 25% higher than predicted) continue to prescribe high in more than half of the intervention bimonthly prescribing periods. This would be interpreted as a lack of effect to the email-based intervention, and a secondary intervention would be offered to all high prescribers consisting of bi-monthly check in with the stewardship lead (either infectious disease pharmacist or medical director of stewardship) at each facility to provide an open forum for questions and answers about the data and any clinical practices.

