## 2. Intervention

The intervention will comprise two components: (1) a one-time educational session on antibiotic de-escalation and (2) bimonthly email feedback reports. Educational sessions, led by facility stewardship leads, will focus on evidence-based recommendations for presumed pneumonia and urosepsis, including indications for empiric anti-pseudomonal coverage and use of the hospital's antibiotic prescribing assistance tool. Feedback reports will reinforce these indications and will provide a link to the tool.

Provider-specific feedback reports will use observed-to-expected ratios (OERs), derived in part from EPIC Clarity System clinical and billing data. Generalized linear models will be used to generate OERs, adjusted for the proportions of patients with sepsis, end-stage renal disease, and urinary tract infections. These risk adjustments will be based on a prior study identifying factors consistently associated with broad-spectrum hospital-onset (BS-HO) antibiotic prescribing (Onwubiko et al. 2024).

Bimonthly, the stewardship research team will automatically email private PDF reports to each provider. Report content and formatting will be informed by CP-FIT's key feedback elements and will be assessed through cognitive interviews with 13 providers conducted during the development phase, with corrective changes to be implemented based on structured interview questions.

One week after the third prescribing report is sequentially sent (six months after intervention initiation), the antibiotic stewardship team will email a single-question Microsoft Form survey to providers, seeking confirmation of whether they viewed the previous reports. Non-responders will receive email reminders from the hospital medicine faculty liaison, who will then personally follow up with remaining non-responders to encourage completion.

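### The only named sensitivity analysis of the primary outcome selects providers on a self-report taken after crossover, so it can introduce bias and should not be described as accounting for it

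*Combined protocol and SAP*

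**What the plan says.** SAP section 7 names one sensitivity analysis for the primary outcome: "Sensitivity analyses of the primary outcome will be conducted among the subset of providers who indicate that they received and reviewed the feedback reports". Its stated purpose is "to account for potential implementation bias".

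Section 7 does not say where the information on review comes from. The only source described is in SAP section 2, where "the antibiotic stewardship team will email a single-question Microsoft Form survey to providers", "seeking confirmation of whether they viewed the previous reports". The timing is "One week after the third prescribing report is sequentially sent (six months after intervention initiation"). The hospital medicine faculty liaison sends reminders to non-responders, "who will then personally follow up with remaining non-responders to encourage completion".

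The SAP gives no expected viewing rate, no rule for classing non-responders, partial viewers or providers who left before the survey, and no method for handling selection after exposure. The primary analysis is not restricted to viewers. However, its exposure term is described as the provider's receipt of reports, without saying that this means the hospital's randomised crossover date.

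**The concern.** Whether a provider belongs to the subset is settled after randomised exposure has begun, by one answer given after three reports on that provider's own prescribing. If reading the reports, or saying that one has read them, is linked to how prescribing moved after crossover, then the subset is chosen partly on the outcome being analysed. Restricting to it would not remove a bias from imperfect implementation. It could add one, in either direction.

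What is at stake is interpretation. As the only sensitivity analysis named for the primary outcome, it is likely to be read as showing the effect where the intervention was taken up. Agreement with the primary result could then be taken as support that it does not provide, and a larger effect among viewers could be taken as evidence of dose-response.

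**Working it through.** **Plan figures.** The documents give no viewing rate and no expected size for the subset, so there is no plan figure to reproduce on this point. The provider count used below comes from SAP section 4: 125 hospitalists, 15 to 40 per hospital, after excluding 11 nocturnists. The stated 8% reproduces: 11 / (125 + 11) = 8.1%.

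**Step 1: does the answer overlap the analysed outcome?** The protocol says that each report covers the previous two months. A third report at six months implies reports at about months 2, 4 and 6, which cover the first three two-month periods after crossover. With the Figure 1 start dates and follow-up to December 2024, the overlap is:

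| Hospital | Start | Post-crossover periods | Covered by the three reports |
|---|---|---|---|
| A | Jul 2023 | 9 | 3/9 = 33% |
| B | Sep 2023 | 8 | 3/8 = 38% |
| C | Nov 2023 | 7 | 3/7 = 43% |
| D | Jan 2024 | 6 | 3/6 = 50% |

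The SAP text allows the last crossover up to 1 March 2024, which would make the last row 3/5 = 60%. At Hospital A the six-month answer governs 9 × 2 = 18 months of intervention data.

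**Step 2: when does this bias the estimate?** Each retained provider keeps their own control periods and has an intercept. A stable tendency to prescribe low therefore appears both before and after crossover and largely cancels. A low value specific to the first post-crossover periods does not cancel, because those periods enter only the exposed side.

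**Step 3: size, by simulation with no true effect.**

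- From the documents: 125 providers in 4 hospitals, 12 two-month periods, the Figure 1 crossovers for A to D, and about 209 billed patient-days per provider-period (437,303 / 116 / 18, from the protocol's preliminary data).
- Assumed: hospital sizes 15/30/40/40, 100 days of therapy per 1,000 billed patient-days, provider SD 0.25 and period-to-period SD 0.25 on the log scale (latter varied 0.15 to 0.40), autocorrelation 0.3 (also 0.6), 62% to 70% viewers, and log-odds of viewing of 0.5, 1 or 2 per SD.
- Fit: log rate on exposure with provider and period effects and provider-clustered standard errors, as a fast stand-in for the negative binomial mixed model. There were 800 runs per scenario.

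| Who says they viewed | Subset mean rate ratio | False positives at nominal 5% |
|---|---|---|
| Random | 1.00 | 5.8% |
| Depends on a stable provider trait | 1.00 | 6.0% |
| More likely after low values in the first three periods (log-odds 0.5, 1, 2) | 0.98, 0.96, 0.94 | 7%, 12%, 21% |
| More likely after a fall from own baseline (0.5, 1, 2) | 0.96, 0.93, 0.89 | 11%, 27%, 61% |
| As above at log-odds 1, varying SD, autocorrelation and provider trends | 0.91 to 0.94 | 24% to 30% |
| More likely after high values (log-odds 1) | 1.05 | 13% |
| Random, with 5% or 10% leavers per year, also with leaving linked to a recent rise | 1.00 | 3.6% to 6.0% |

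Keeping every provider and coding exposure by hospital crossover gave 0.999 to 1.003, with 4.6% to 5.9% false positives, in all of these scenarios (Monte Carlo error about 1.5 points). The simulation has no hospital-specific time shocks, so this last figure does not show that the primary model controls error with four clusters.

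**Step 4: check with a mixed model.** A smaller run (60 trials per scenario, residual SD 0.35, hospital SD 0.1) fitted a random-effects model to viewers only.

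- 80% viewing among below-median and 50% among above-median prescribers: log estimate −0.030 (simulation SE 0.008), about −3%.
- 90% against 30%: −0.052, about −5%.
- 50% against 80%: about +2.5%.
- 65% in both groups: about 0.

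The directions agree with Step 3.

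**Step 5: what rescaling can and cannot do.** If L is the all-provider log rate ratio and p the share viewing, the effect of viewing is estimated by L/p. With p treated as known, its standard error is SE/p, so z = (L/p)/(SE/p) = L/SE. Neither the sign nor the p-value can change. For illustration, a rate ratio of 0.90 (L = −0.105) with p = 0.70 gives exp(−0.151) = 0.86. With p = 0.62 it gives exp(−0.170) = 0.84.

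**The case against.** The strongest reply is that the bias is conditional and the documents do not show that its condition is met. This stands. Nothing in them says that viewing follows prescribing, and random or trait-driven viewing gives no bias. The reports are private PDFs, and if their content is unknown before opening, the decision to open the first one cannot depend on what it shows. Selection on all three windows is therefore a strong assumption, and the larger simulated biases sit at that end. The reports also show observed-to-expected ratios from hospital-specific models, whereas the simulations select on the log rate. The single answer does, however, come after all three reports, so later viewing and the answer itself can still depend on them.

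It is also fair that this is a labelled sensitivity analysis, that no decision rule uses it and that the primary analysis is unrestricted. This limits the consequence to how the result is read.

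Four stronger readings are tempting and are not supported:

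- **Leavers.** A reader might infer that dropping early leavers itself creates a false effect. The SAP does not say how leavers are classed, it expects turnover of at most 10% (period not stated), and dropping about 9 to 18 leavers before the survey left the simulated rate ratio at 1.00.
- **The liaison.** A reader might infer that providers declare viewing face to face. They answer a form from the stewardship team, and the liaison only pursues non-responders.
- **The Top Performer label.** This is protocol content described there as still under development, and the SAP's account of the reports does not mention it. It illustrates a possible mechanism and is not evidence of one.
- **Rescaling as a bound.** Dividing by the viewing share might look like an upper bound on the effect of viewing. Over-reported viewing makes the share too high and the result too small. Counting true viewers among the non-responders as non-viewers, or an effect of the educational session on non-viewers, pushes the other way.

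**Conclusion.** The concern holds in conditional form. The subset is defined by self-report after exposure, overlaps the analysed outcome periods and comes with no method for selection, so the claim that it accounts for implementation bias is unsupported. If viewing, or saying so, tracks prescribing after crossover, a null intervention can yield a mean rate ratio of about 0.89 to 1.05 in the subset. If viewing is random or follows only a stable trait, it yields 1.00.

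That range rests on assumed variances and viewing patterns, so it shows what is possible and does not predict this trial. For scale, the protocol refers to a 10% reduction, but that belongs to its 147-provider plan with a standardised ratio as endpoint. The SAP gives no target for its own outcome. Nothing here implies that the primary analysis is biased by viewing. The point is one the plan should correct, and it bears on what may be concluded from agreement between the two analyses.

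**What to change.** In SAP section 7:

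1. State that the effect estimate keeps all listed providers, with exposure coded by their hospital's randomised crossover and not by individual receipt or viewing.
2. Delete the bias-correction phrase. Label the viewer-only result exploratory, and say that it does not confirm the primary result.
3. State how survey non-responders and providers who left before the survey are classed.
4. Report the share viewing, and baseline prescribing by viewer status, for each hospital.
5. If an effect of viewing is wanted, use a complier-type estimate with randomised crossover as the instrument. State its assumptions: no effect on non-viewers, which the educational session may violate, and accurate self-report. Do not call it an upper bound or treat its agreement with the primary result as independent support, since by construction it shares that result's sign.

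The cost is SAP wording and a small extra analysis on data already being collected. The estimate for viewing will have a wider interval than the all-provider estimate.
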